### Ethical Considerations

The study will be conducted according to the Declaration of Helsinki (Hong Kong Amendment) [94]. The study participants will be made to provide informed consent before their inclusion in the study. The research team will strictly adhere to the protection of participants’ health information according to the structure laid down by the 2 major health institutions (Alberta Health Services and Nova Scotia Health Authority). An independent monitor will be assigned by the research team to monitor the progress of the research, ensure the completeness of informed consent and data safety, and liaise with the ethics committee. Although not anticipated, serious adverse events will be reported to the Research Ethics Committee. The study has received ethical clearance from the Health Ethics Research Board of the University of Alberta (Pro000122696) and the Nova Scotia Health Research Ethics Board (REB File #: 1028488).

## Results

The study is registered at ClinicalTrials.gov (registration number: NCT05570344). The study is yet to commence recruitment of participants. The study results are envisioned to be available 18 months from the start of recruitment. The results are expected to be disseminated at different levels, including practitioners, health care organizations, and academics/researchers. Before the study ends, the team of investigators will organize an engagement plan to discuss the practicability and effectiveness of the study.

## Discussion

### Overview

The findings from the study will provide the data needed to assess the initial effectiveness of rTMS plus Text4Support for individuals diagnosed with TRD. Though there are several pieces of evidence in the literature in support of the effectiveness of rTMS in TRD, the data generated regarding rTMS application are relevant only when it is used as a single treatment modality. However, the concomitant application of psychotherapy with rTMS is limited. Therefore, we hope that this novel project will provide a concrete base of data to enable the evaluation of the wider-scale practical application and efficacy of the combination of rTMS and Text4Support. To the best of our knowledge, this study will be the first clinical trial to investigate the combined effect of these 2 interventions. Owing to the limited availability of data regarding this specific area of treatment, another objective will be to generate effect size information for these interventions to aid future power and sample size calculations for a full-scale RCT.

### Strengths of This Study

This study has several strengths. First, since this RCT will be conducted in a naturalistic clinical care setting, translation of the results to clinical practice will be easier. Regardless of the outcome of this trial, the findings can inform clinical decision-making and aid in choosing the right treatment for a patient with TRD. Second, this study will have a longer follow-up duration than other rTMS trials. Since data up to 6 months from the start of the study will be available, the durability of the treatment effects of rTMS in the longer term can be evaluated. Third, randomizing participants will ensure that participants in the 2 treatment arms have similar psychiatric morbidity at baseline. Moreover, the blinding of all primary outcome assessors to the primary outcome measures will ensure the elimination of rater bias in the outcome measures.

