**Objective:**

This study aims to assess the initial comparative clinical effectiveness of rTMS with and without the Text4Support program as an innovative patient-centered intervention for the management of patients diagnosed with TRD.

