## Methods

### Study Design and Setting

This study is a multicenter, prospective, parallel design, 2-arm, rater-blinded randomized controlled pilot trial. Participants will be randomly assigned to 1 of 2 treatment conditions. The first condition includes rTMS sessions combined with Text4Support. The second condition includes treatment as usual (rTMS sessions alone). The recruitment process is scheduled to last 12 months. It will involve active treatment for 6 weeks and follow-up with observation periods of 6 weeks, and 3 and 6 months for participants in both arms of the study. Figure 1 presents the CONSORT (Consolidated Standards of Reporting Trials) flowchart for the project. Participants will be recruited from 4 different centers for this project. Two centers (the Addiction and Mental Health Clinic and the Alberta Day Hospital) are from the large sociodemographically diverse city of Edmonton in Alberta, Western Canada. The remaining 2 centers are in Halifax and Annapolis Valley in Nova Scotia, Canada. Table 1 presents the proposed timelines for this project.

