### Sample Size Calculation

This study is a pilot study with no standardized data documented on the effect size, which could aid in power and sample size calculations. We will therefore use data that can be generated from the study participants recruited within the existing protocol. This approach is accepted for pilot studies that consist of novel interventions, such as this, and this method has been described by Haynes et al [85] as using “the participants I can get.” In this regard, the study will be limited to a sample size of about 200 (120 from Edmonton and 80 from Halifax), with 100 participants recruited in each of the study arms. Since TRD is characterized by periods of relapses and depressive attacks, we anticipate a certain number of eligible patients to decline to enroll in the study or even drop out before the completion of the study.

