All MT assessments will be conducted by the rTMS team of experts within the rTMS clinics in the various treatment centers, and the team may involve psychiatrists, nurses, and other health care professionals with the requisite training to perform the assessments. Each TMS assessment session will take about 3 to 5 minutes, and the total time will be within 35 to 45 minutes. This visit timeline will be the same for all study participants. Overall, all study participants will be scheduled to receive 30 sessions of rTMS treatment for 6 weeks according to the schedule pre-established by the Alberta Health Services’ Strategic Clinical Network for Addiction and Mental Health and Nova Scotia Health. The rTMS protocol includes low-frequency (1 Hz) inhibitory stimulation targeting the right dorsolateral prefrontal cortex at 120% MT, with 20 trains (60 pulses/train at 60 s) and a total pulse of 1200 for 20 minutes, and high-frequency (10 Hz) excitatory stimulation targeting the left dorsolateral prefrontal cortex at 120% MT, with 75 trains (intertrain interval of 11 s) and a total pulse of 3000 for 19 minutes. The study will use the MagVenture rTMS machine with a figure-of-8 coil. The angle between the coil and the head will be measured at 45 degrees. The cortex area will be targeted by using the 5-cm technique. The prefrontal cortex stimulation site will be determined as 5 cm anterior further ahead of the motor strip in the parasagittal line. Regarding the issue of adherence to the treatment protocol, the rTMS team of experts will contact each patient to remind them of their sessions whenever they default in order to ensure adherence to the treatment. The patients will be continuously monitored, and an attending nurse will remain with each patient during the whole session, checking on any expected side effects. Complete treatment will be considered as attending at least 25 out of 30 sessions.

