### Data Analysis

SPSS Version 26 (IBM Corp) will be used to analyze all quantitative data in accordance with the CONSORT guidelines [92]. Following an intention-to-treat approach, data will be analyzed with descriptive statistics, repeated measures, and correlational analyses. Descriptive data for baseline parameters will be presented using frequencies and percentages among the 2 intervention groups and compared using the chi-square test for categorical variables and the independent sample *t* test for continuous variables. The type of intervention (rTMS alone and rTMS plus Text4Support) will be considered the independent variable, while the scores of the various scales at each time point (6 weeks, and 3 and 6 months) will be considered the dependent variables for each of the analyses. Baseline scores of the respective scales will be used as covariates in the analyses.

To compare the effectiveness of the treatment interventions for the management of TRD among participants, the 1-way between-group analysis of covariance (ANCOVA) comparing changes in the mean scores from baseline to 6 weeks, and 3 and 6 months for all measures will be employed. Preliminary checks will be conducted to ensure there is no violation of the assumption of normality, linearity, homogeneity of variance, homogeneity of regression slopes, or reliable measurement of the variate before ANCOVA is conducted. For participants with missing data, the last observation will be imputed before performing sensitivity analyses of covariance to explore the impact of the imputation of data loss on the PHQ-9 and the secondary measures at each time point.

The chi-square test or Fisher exact test will be employed to compare the prevalence of depression symptoms using the PHQ-9, the prevalence of anxiety symptoms using the GAD-7, suicidal ideations using the CSSRS, and quality of life using the WHO-5 between the 2 intervention groups at all time points in the overall sample.

Furthermore, a paired *t* test will be used to examine the changes in the mean scores of the PHQ-9, GAD-7, CSSRS, and WHO-5 at baseline and 6 weeks for participants who complete the instruments at both time points. Frequencies and percentages will be used to report categorical variables, while mean scores, confidence intervals, and effect sizes will be used to report continuous variables. The 2-tailed α-level criterion for statistical significance will be set at *P*≤.05.

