### Limitations

As eligible patients will ultimately decide on whether they want to join the study, a major limitation may be selection bias, which will potentially result in the selection of highly motivated patients. This may affect the ability to achieve a good study sample size and power. Another limitation may be associated with possible variabilities in illness duration and concomitant treatments being received by patients outside the rTMS treatment, which could have confounding effects on the outcomes of our interventions.

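### The 6-month follow-up is said to show how long rTMS effects last, but both arms receive rTMS, so randomisation identifies only the added effect of Text4Support

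*Protocol article*

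**What the plan says.** The Objective is to assess the "comparative clinical effectiveness of rTMS with and without the Text4Support program". Study Design and Setting defines two arms. "The first condition includes rTMS sessions combined with Text4Support"; the second is rTMS alone, labelled treatment as usual. Interventions states that "all study participants will be scheduled to receive 30 sessions of rTMS treatment for 6 weeks", so the course does not differ by arm. Sample Size Calculation plans about 200 participants, "with 100 participants recruited in each of the study arms".

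Data Analysis takes arm as the independent variable and compares the arms by ANCOVA, with the baseline score as covariate, at 6 weeks, 3 months and 6 months. It adds a paired t test of baseline against 6 weeks, "for participants who complete the instruments at both time points".

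Strengths of This Study then says that, with data to 6 months, "the durability of the treatment effects of rTMS in the longer term can be evaluated". Limitations names variable illness duration and "concomitant treatments being received by patients outside the rTMS treatment" as possible confounders. It does not say that the effect of rTMS itself cannot be estimated.

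**The concern.** The sentence in Strengths of This Study credits the trial with evaluating a treatment effect of rTMS. A treatment effect is a difference from what would have happened without the treatment, and the trial has no group that goes without rTMS. Extending follow-up to 6 months does not supply one.

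What is at stake is interpretation. The same section says the findings can inform clinical decisions in TRD, and the Introduction and Discussion plan to use the trial's effect sizes to plan a full-scale trial. A reader who takes the sentence at its word could treat improvement still present at 6 months as a lasting rTMS effect and carry it into either use. Persistence of benefit matters in this population: the Background cites relapse in about 80% of patients with TRD within 1 year of remission.

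**Working it through.** The plan gives no figure to reproduce, and the point needs none. It is a check of which quantities the design can identify.

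**Inputs**
- rTMS exposure: the same schedule in both arms, 30 sessions over 6 weeks (Interventions).
- Difference between arms: presence or absence of Text4Support only (Study Design and Setting; Interventions).
- Comparator without rTMS: none described.
- Analysis variable: arm, at 6 weeks, 3 months and 6 months (Data Analysis). Table 2 gives the first follow-up as 1 month; the argument is the same for either time.

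**Notation**, for mean change from baseline to time t:
- m(t): change that would occur without rTMS or Text4Support (natural course, regression to the mean, concomitant treatment, non-specific effects).
- R(t): effect of rTMS.
- T(t): effect of adding Text4Support to rTMS, including any interaction between the two.

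**Step 1. What each arm estimates**
- rTMS alone: m(t) + R(t)
- rTMS plus Text4Support: m(t) + R(t) + T(t)

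**Step 2. The randomised contrast**

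[m(t) + R(t) + T(t)] − [m(t) + R(t)] = T(t)

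R(t) drops out at every time point. More participants or longer follow-up would sharpen or extend the estimate of T(t), but neither brings R(t) back.

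**Step 3. The within-arm route**

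The rTMS-alone arm shows only the sum m(t) + R(t). Suppose scores at 6 months stay at their 6-week level. That fits a lasting R(t) with stable m(t), and equally a fading R(t) offset by spontaneous recovery or by a new treatment begun after the rTMS course. The data cannot tell these apart. Limitations itself accepts that treatment outside rTMS may influence outcomes.

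**Step 4. What the stated analyses cover**

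The ANCOVAs at 3 and 6 months estimate T(t). The only within-participant test spelled out, the paired t test, ends at 6 weeks, before the period over which durability would be judged. Data Analysis also mentions repeated measures without detail, but no within-arm model could separate R(t) from m(t) in this design.

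**Step 5. What the design does support**

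Text4Support messages run for 6 weeks (Interventions). T(t) at 3 and 6 months is therefore a randomised measure of how long the added effect of Text4Support lasts after the messages stop.

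**The case against.** The strongest reply is that the sentence promises evaluation, not a controlled or causal estimate. The rTMS-alone arm, about 100 people with no Text4Support, can show whether improvement seen at 6 weeks is still present at 3 and 6 months. That is useful, and it stands as a description. It does not rescue the sentence, which speaks of treatment effects of rTMS in a list that also cites randomisation as a strength, while Limitations gives no counterweight.

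A second reply is that this is one sentence in the Discussion. That also stands. The Objective, the Hypothesis and the ANCOVA all concern rTMS with against without Text4Support, and the sentence changes no comparison, test, visit or sample size.

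Some stronger inferences are tempting, but the documents do not support them:
- *That the plan will report within-arm change at 3 and 6 months as a lasting rTMS effect.* No within-arm test is stated for those times, and the paired t test is not attributed to rTMS.
- *That carrying the last observation forward inflates apparent durability.* Data Analysis ties that imputation to sensitivity ANCOVAs, which compare arms; nothing feeds it into a within-arm durability estimate.
- *That the share of improvement due to regression to the mean can be put in PHQ-9 points.* The article gives no PHQ-9 standard deviation, test-retest correlation in this population or PHQ-9 entry threshold. Regression to the mean would also bear mainly on the fall from baseline, whereas durability concerns what happens after 6 weeks.

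**Conclusion.** The claim in Strengths of This Study is wrong as written: it states a property the design does not have. The trial can evaluate the durability of the added effect of Text4Support. It can describe, but not attribute, the course of symptoms after rTMS. The weight of the rTMS effect in the randomised contrast is exactly zero at every time point. That conclusion rests only on both arms receiving the same rTMS course and on there being no rTMS-free group, both of which can be read from the article; it needs no assumed figure.

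A reader might infer that the trial design or its primary analysis is at fault. It is not: the two arms suit the stated objective, and the between-arm PHQ-9 comparison is untouched. The defect is confined to what the article says may be concluded.

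**What to change.** In Strengths of This Study, replace the sentence on rTMS durability with wording such as:

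> The trial can evaluate the durability to 3 and 6 months of the added effect of Text4Support, as the between-arm difference in PHQ-9; the course of symptoms after rTMS within arms will be described but not attributed causally to rTMS.

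In Limitations, add that no group goes without rTMS, so the effect of rTMS itself, and how long it lasts, cannot be estimated from this trial.

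The cost is wording and the loss of one claimed strength. No arm, visit, sample size or analysis changes. The Results section says recruitment has yet to begin, so the correction can be made before any data exist.

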### Limitations

As eligible patients will ultimately decide on whether they want to join the study, a major limitation may be selection bias, which will potentially result in the selection of highly motivated patients. This may affect the ability to achieve a good study sample size and power. Another limitation may be associated with possible variabilities in illness duration and concomitant treatments being received by patients outside the rTMS treatment, which could have confounding effects on the outcomes of our interventions.

## Abbreviations

ANCOVA: analysis of covariance
BDI-II: Beck Depression Inventory-II
CONSORT: Consolidated Standards of Reporting Trials
CSSRS: Columbia-Suicide Severity Rating Scale
GAD-7: 7-item Generalized Anxiety Disorders Scale
MDD: major depressive disorder
MT: motor threshold
PHQ-9: Patient Health Questionnaire-9
RCT: randomized controlled trial
rTMS: repetitive transcranial magnetic stimulation
TMS: transcranial magnetic stimulation
TRD: treatment-resistant depression
WHO-5: World Health Organization-Five Well-Being Index
